## Abstract

**Background:**

[^18^F]Fluorodeoxyglucose ([^18^F]FDG) positron emission tomography (PET) is recommended during diagnostic work-up for ovarian cancer; however, [^18^F]FDG PET has several inherent limitations. The novel oncologic PET-tracer fibroblast activation protein inhibitor (FAPI) has demonstrated promising results in multiple cancer types, including ovarian cancer, and could overcome the limitations of [^18^F]FDG PET; however, high-quality clinical studies are lacking. The primary objective of the present study is to compare the diagnostic accuracy of [^68^Ga]Ga-FAPI-46 PET/CT and [^18^F]FDG PET/CT in ovarian cancer patients and to investigate how this potential difference impacts staging and patient management.

**Methods and design:**

Fifty consecutive ovarian cancer patients will be recruited from Aalborg University Hospital, Denmark. This study will be a single-center, prospective, exploratory clinical trial that adheres to the standards for reporting diagnostic accuracy studies (STARD). This study will be conducted under continuous Good Clinical Practice monitoring. The eligibility criteria for patients are as follows: (1) biopsy verified newly diagnosed ovarian cancer *or* a high risk of ovarian cancer *and* referred for primary staging with [^18^F]FDG PET/CT; and (2) resectable disease, i.e., candidate for primary debulking surgery *or* neoadjuvant chemotherapy followed by interval debulking surgery. All recruited study subjects will undergo [^68^Ga]Ga-FAPI-46 PET/CT at primary staging, before primary debulking surgery or neoadjuvant chemotherapy (Group A + B), in addition to conventional imaging (including [^18^F]FDG PET/CT). Study subjects in Group B will undergo an additional [^68^Ga]Ga-FAPI-46 PET/CT following neoadjuvant chemotherapy prior to interval debulking surgery. The results of the study-related [^68^Ga]Ga-FAPI-46 PET/CTs will be blinded, and treatment allocation will be based on common clinical practice in accordance with current guidelines. The histopathology of surgical specimens will serve as a reference standard. A recruitment period of 2 years is estimated; the trial is currently recruiting.

**Discussion:**

To our knowledge, this trial represents the largest, most extensive, and most meticulous prospective FAPI PET study conducted in patients with ovarian cancer thus far. This study aims to obtain a reliable estimation of the diagnostic accuracy of [^68^Ga]Ga-FAPI-46 PET/CT, shed light on the clinical importance of [^68^Ga]Ga-FAPI-46 PET/CT, and examine the potential applicability of [^68^Ga]Ga-FAPI-46 PET/CT for evaluating chemotherapy response.

**Trial registration:**

clinicaltrials.gov: NCT05903807, 2nd June 2023; and euclinicaltrials.eu EU CT Number: 2023-505938-98-00, authorized 11th September 2023.

## Background

In Europe, ovarian cancer (OC) ranks as the fifth leading cause of death among female cancer-related fatalities. In 2020, 27,138 new cases were reported, accounting for 4.9% of all female cancer deaths [1]. Seventy-to-80% of all OC patients are diagnosed at advanced stages because symptoms are discrete and often caused by peritoneal metastases [2]. Early detection and complete cytoreduction (no visible disease, R0 resection) or optimal cytoreduction (leaving tumor nodules < 1 cm, R1 resection) are crucial for treatment and survival [3, 4]. Treatment for OC involves curatively intended primary debulking surgery (PDS) followed by adjuvant systemic chemotherapy; however, in advanced stages where complete cytoreduction by PDS is unlikely, interval debulking surgery (IDS) after 2–3 cycles of neoadjuvant chemotherapy (NACT) is the preferred treatment option [5].

Imaging modalities play a crucial role in the clinical work-up of OC patients and are fundamental for efficient diagnosis and correct patient management. In summary, ultrasound (US) is essential for screening and diagnosis, while magnetic resonance imaging (MRI), computer tomography (CT), and [^18^F]fluorodeoxyglucose positron emission tomography ([^18^F]FDG PET) are useful in evaluating the extent of disease [6–9]. Moreover, multiple imaging-based models have been proposed for the preoperative prediction of cytoreducibility. Although these models provide clinically useful information, no single imaging-based prediction model is adequate for accurately predicting the outcome of a surgical procedure [10–13].

[^18^F]FDG PET/CT, an imaging modality visualizing elevated glycolysis, is a highly valuable tool in OC, as it can improve the efficacy of OC diagnosis, recurrence detection, staging and prognosis. In particular, this imaging modality has high sensitivity for detecting lymph node metastases and extra-abdominal metastases [14–21]. However, [^18^F]FDG PET has several limitations. First, [^18^F]FDG is suboptimal for discerning borderline tumors from benign tumors [16, 17]. Second, [^18^F]FDG uptake is low in certain histological subtypes, i.e., mucinous, clear-cell and cystic carcinomas [22]. Third, false-positive [^18^F]FDG PET uptake in ovaries can be observed in several benign ovarian conditions [23, 24]. Moreover, many benign conditions can be misinterpreted as peritoneal or distant organ metastases [21, 25]. Fourth, the predictive value of [^18^F]FDG PET for determining the likelihood of achieving complete cytoreduction is limited [20, 26–28]. Also, malignant peritoneal lesions demonstrate varying [^18^F]FDG uptake, leading to suboptimal performance in predicting peritoneal carcinomatosis and/or predicting the outcome of surgery [13, 29].

[^18^F]FDG PET imaging plays a crucial role in the diagnostic evaluation of OC and is recommended in guidelines [5, 30]; however, to optimize the diagnostic performance of PET in OC, it is necessary to overcome the inherent limitations of the tracer [^18^F]FDG.

Fibroblast activation protein (FAP) is a transmembrane protein that can be upregulated in solid tumors, including epithelial carcinomas [31–33]. In most tumors in which FAP is present, FAP is not directly expressed by the cancer cells themselves but by cancer-associated fibroblasts (CAFs), which represent a major part of the gross tumor volume. In 2018, the first results of [^68^Ga]Ga-FAPI PET/CT were published, with promising results both in animal cancer models and in cancer patients [32, 34, 35]. In pathological studies of human cancer tissue, FAP expression has been detected in 85–97% of ovarian cancers, both in serous and mucous subtypes. Moreover, FAP is absent/low in normal ovarian tissue and under benign conditions [33, 36–38]. Immediately after the development of the FAPI, the clinical value of FAPI PET/CT in OC patients was highlighted by several case reports in which FAPI PET/CT detected far more peritoneal metastases than [^18^F]FDG PET/CT [39–41]. Additionally, FAPI uptake in ovaries does not seem to be affected by the menstrual cycle, as is the case with [^18^F]-FDG [42, 43].

Only recently have cohort studies been conducted on ovarian cancer. In a retrospective study of nonconsecutive patients, FAPI PET/CT outperformed FDG PET/CT in terms of sensitivity for primary tumors (100% vs. 78%), lymph nodes (100% vs. 80%) and peritoneal metastases (100% vs. 56%). In this study, 36% of newly diagnosed ovarian cancer patients were correctly upstaged on FAPI PET/CT due to missed lesions on [^18^F]FDG PET/CT [44]. Another retrospective study confirmed that, compared with FDG PET/CT, [^68^Ga]Ga-FAPI-04 PET/CT correctly detected twice the number of peritoneal metastases [45]. In a study of patients with suspected relapse of OC, [^68^Ga]Ga-FAPI-04 PET/CT outperformed [^18^F]FDG PET/CT (overall pooled lesion sensitivity: 96% vs. 49%), and the chosen treatment was altered in 17% of the patients [46]. In a prospective study by Chen et al., [^68^Ga]Ga-FAPI-04 PET/CT and [^18^F]FDG PET/CT demonstrated equivalent sensitivities for primary tumors (approximately 92–94%) but significantly greater sensitivities for [^68^Ga]Ga-FAPI-04 PET when assessing lymph node metastases and peritoneal metastases (81% vs. 61% and 98% vs. 76%, respectively), leading to upstaging in 14% of treatment-naïve patients and 33% of relapsed patients and a change in treatment in 11% of treatment-naïve patients and 19% of relapsed patients [47]. However, according to the results of another prospective study, [^68^Ga]Ga-FAPI PET/CT and [^18^F]FDG PET/CT demonstrated comparable sensitivities for primary tumor and lymph node metastases (approximately 90–100% for both tracers), and [^68^Ga]Ga-FAPI PET/CT had only slightly better sensitivity for peritoneal lesions [48].

Although most reports on FAPI PET in patients with ovarian cancer seem convincing, there are several limitations, including relatively small cohorts and mostly retrospective study designs. The few prospective studies performed do not include consecutive patients, and most findings (beyond the primary tumor) are not comparable to a histopathological reference standard. Moreover, the effect of chemotherapy on FAPI uptake and the feasibility of using FAPI PET/CT for evaluating patient response after NACT are unknown. These latter concepts are highly relevant because approximately 75% of OC patients are diagnosed at advanced stages and undergo interval cytoreductive surgery following neoadjuvant chemotherapy [49]. Studies overcoming these limitations are therefore needed before randomized trials using FAPI PET/CT can be designed to implement FAPI PET in clinical practice for the potential benefit of future cancer patients.

By conducting the present comparative diagnostic accuracy study of [^68^Ga]Ga-FAPI-46 PET/CT and [^18^F]-FDG PET/CT in OC, we aim to answer several of these questions, providing a significant contribution to the rapidly evolving field of diagnostic [^68^Ga]Ga-FAPI-46 PET in OC and other cancer entities.

## Methods and design

### Study characteristics and identification

The present study will be a single-center, prospective, explorative clinical trial investigating the diagnostic accuracy and clinical value of the novel, oncologic, diagnostic PET tracer [^68^Ga]Ga-FAPI-46 in patients with newly diagnosed ovarian cancer. The study protocol has been uploaded to clinicaltrials.gov (NCT05903807) and euclinicaltrials.eu (EU CT: 2023-505938-98-00. The study will take place in its entirety at Aalborg University Hospital (Aalborg UH), Denmark.

### Study objectives

#### Primary objectives

The primary objectives are to compare the FAPI PET/CT and FDG PET/CT findings in primary tumors, regional lymph nodes and distant metastases to a histopathological reference standard to the sensitivity, specificity, positive predictive value (PPV), and negative predictive value (NPV) of the PET/CTs, both at primary staging and post-NACT staging (i.e., staging after NACT, prior to interval debulking). This will include a comparison of the cancer stage determined by FAPI PET/CT and conventional imaging (including [^18^F]FDG PET/CT) at primary staging and post-NACT staging [50, 51]. The proportions of patients downstaged, having unchanged stage, and being upstaged according to the added FAPI PET/CT will be determined.

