### Secondary objectives

The secondary objectives are as follows: (1) To estimate the proportion of patients hypothetically treated differently due to [^68^Ga]Ga-FAPI-46 PET/CT replacing [^18^F]FDG PET/CT; (2) to investigate the intensity of [^68^Ga]Ga-FAPI-46 uptake in tumor deposits; (3) to investigate the feasibility of FAPI PET/CT for chemotherapy-response assessment compared to FDG PET/CT; (4) to investigate the prognostic value of FAPI PET/CT compared to FDG PET/CT at primary staging and post-NACT staging; (5) to evaluate potential unexpected FAPI PET/CT findings; and (6) to evaluate the safety of [^68^Ga]Ga-FAPI-46 injections.

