**Fig. 1 Fig1:**
[figure not shown]
FAPI PET in ovarian cancer study design and flow

[^68^Ga]-Ga-FAPI-46 PET/CT data will be interpreted after enrollment of all patients and compared to the [^18^F]-FDG PET/CT data. Histopathology of the resected specimens and biopsies will serve as a reference standard for calculating the diagnostic accuracy. For suspicious lesions not confirmed by histopathology, other imaging modalities (US, MRI, CT), biochemistry, and medical records will be used for classification. The clinical impact of [^68^Ga]Ga-FAPI-46 PET/CT, both at primary staging and post-NACT staging, will be evaluated at a retrospective tentative MDT with the participation of an onco-gynecological surgeon, an oncologist, a pathologist, and a nuclear medicine physician, all of which specialize in the treatment of ovarian cancer. The tentative MDT will be performed retrospectively and therefore has no influence on the actual treatment of patients; moreover, the MDT differs from the clinical MDT, as clinicians will present study-related [^68^Ga]Ga-FAPI-46 PET/CTs instead of [^18^F]FDG PET/CTs. The study flow is depicted in Fig. 1.

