### Staging and impact on patient management

Tentative staging based on FAPI and [^18^F]FDG PET/CT data will be performed according to the International Federation of Gynecological Oncology’s classification system (FIGO) and the American Joint Committee on Cancer (AJCC 8th) edition TNM classification. Staging, as determined at the tentative MDT, will be compared for [^68^Ga]Ga-FAPI-46 PET/CT and [^18^F]FDG PET/CT, both at primary staging and post-NACT staging, and patients will be classified as “upstaged”, “unchanged”, or “downstaged” due to [^68^Ga]Ga-FAPI-46 PET/CT. The proportions of patients in these categories will be calculated. Furthermore, at the tentative MDT, the treatment strategy (e.g., operability, resectability, palliative treatment, other treatment) will be evaluated purely based on the [^68^Ga]Ga-FAPI-46 PET/CTs (replacing [^18^F]FDG PET/CTs) both at primary staging and at post-NACT staging. The proportion of patients with a hypothetically changed treatment strategy will be calculated. Supplementary imaging results (excluding the FDG PET/CT results), biochemical data, and medical records prior to the staging time point will be available for the clinicians attending the tentative MDT to mimic the situation at the clinical MDT.

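### The stage-shift part of the primary objective counts patients moved up, down or not at all, but never checks the stage against pathology, so it cannot show which tracer stages better

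*Protocol article*

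**What the plan says.** - **Primary objectives.** Both PET/CTs are compared with a histopathological reference for sensitivity, specificity, PPV and NPV. The section then continues: "This will include a comparison of the cancer stage determined by FAPI PET/CT and conventional imaging", the latter including FDG PET/CT, at primary and post-NACT staging. The summary measure is: "The proportions of patients downstaged, having unchanged stage, and being upstaged according to the added FAPI PET/CT will be determined".
- **Staging and impact on patient management.** Stage is taken from the tentative MDT and compared between the two tracers. Each patient is labelled upstaged, unchanged or downstaged due to FAPI, and: "The proportions of patients in these categories will be calculated". No reference stage is named.
- **Study flow overview (text after Fig. 1).** Histopathology of resected specimens and biopsies is the reference for diagnostic accuracy. At the tentative MDT the procedure differs from the clinical one, "as clinicians will present study-related [^68^Ga]Ga-FAPI-46 PET/CTs instead of [^18^F]FDG PET/CTs".
- **Background.** One retrospective study is cited because 36% of newly diagnosed patients "were correctly upstaged on FAPI PET/CT due to missed lesions" on FDG. A prospective study is cited for upstaging in 14% of treatment-naïve patients.
- **Sample size and patients.** The target is 50 confirmed ovarian cancers, about 25 going directly to surgery (Group A) and about 25 to NACT first (Group B).

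**The concern.** A stage shift is a disagreement between two imaging-based stages. It does not say which one was right. If FAPI shows a lesion that FDG missed and the lesion is malignant, the upstaging is an improvement. If the lesion is benign, the upstaging is an error. The planned categories record both as upstaged. Downstaging has the same ambiguity: a false FDG finding correctly removed and a true lesion missed by FAPI fall in one cell.

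The lesion-level accuracy analysis does not close this gap. A false-positive deposit may leave the stage unchanged where more extensive disease is present, or may move the patient to another stage. Whether the patient's stage was right has to be tabulated per patient. The article itself quotes earlier work by the share correctly upstaged, and faults earlier studies because most findings beyond the primary tumor lacked a histopathological comparison. Its own staging outcome omits that comparison.

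**Working it through.** The article gives no expected shift proportion, precision target or error rate for this outcome, and it says that no formal sample size calculation was feasible. There is no stated figure to reproduce. The check is what a shift proportion can and cannot determine.

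**Algebra.** Among n patients with a known true stage, each shifted patient belongs to one of three groups:
- b: FAPI stage right, FDG-based stage wrong
- c: FDG-based stage right, FAPI stage wrong
- d: both wrong

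Patients with unchanged stage have the same stage under both tracers, so both are right or both are wrong, and they add nothing to the difference. Therefore:

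- reported shift proportion = (b + c + d)/n
- difference in proportion correctly staged, FAPI minus FDG = (b - c)/n

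The plan reports the first, split by direction. The second cannot be recovered from it.

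**Illustration.** Inputs: n = 50 (Sample size and patients), and upstaging proportions of 14% and 36% (Background). The share p of shifts that are correct is an assumption, varied over its full range. For simplicity, d = 0 (exactly one of the two stages is right in each shifted patient) and only upstagings are counted. With x upstaged, the net change is [x·p - x·(1 - p)]/50.

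| Upstaged | Exact 95% CI | p = 1 | p = 0.5 | p = 0 |
|---|---|---|---|---|
| 7/50 = 14% | 5.8% to 26.7% | +14 points | 0 | -14 points |
| 18/50 = 36% | 22.9% to 50.8% | +36 points | 0 | -36 points |

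For example, at x = 7 and p = 1 the result is 7/50 = +14 points; at p = 0 it is -7/50 = -14 points. Allowing d > 0 moves the result toward zero but does not fix its sign. The confidence interval describes only how often stage changes, not whether the change was right.

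**Precision of the proposed check.** With about 25 Group A patients, an observed 4/25 (16%) has an exact 95% CI of 4.5% to 36.1%, and 9/25 (36%) one of 18.0% to 57.5%. The check would be imprecise, but it would address the right quantity.

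**The case against.** **The outcome is descriptive and the trial exploratory.** The categories are neutral, no hypothesis test is attached, and false-positive FAPI findings are captured in the lesion-level accuracy results of the same objective. A condensed article may also leave a cross-tabulation to the full protocol. This stands as a reason for moderate weight. A reader might infer that the plan treats upstaging as a benefit, but the documents nowhere say so. What remains is that the article does fix the output measure of this outcome, and that measure has no reference stage.

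**Pathology cannot give the primary stage in everyone.** In Group B surgery follows NACT, so specimens may not reflect the stage at first imaging. This stands and limits the fix.

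**Add-on versus replacement.** A reader might infer a stronger fault: that the objective defines FAPI as added to conventional imaging while the methods replace FDG, so that a primary result depends on which section the analyst follows. The documents do not support that. Study flow overview uses additional simply for the extra study scan, and the sentence before the quoted one in Primary objectives is head-to-head. The only procedure described shows FAPI in place of FDG, with FDG results withheld; no combined reading is described. The phrases "hypothetically treated differently due to [^68^Ga]Ga-FAPI-46 PET/CT replacing [^18^F]FDG PET/CT" and "replacing [^18^F]FDG PET/CTs" concern treatment strategy, not stage shift. This is loose wording.

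**Sizing that conflict.** It is tempting to take the cited nodal sensitivities (FAPI 81%, FDG 61%) and compute 0.61 × (1 - 0.81) = 11.6% of node-positive patients open to downstaging under replacement and about none under add-on. That assumes independent readings although contrast-enhanced CT is available to readers of both tracers. It treats the sensitivities as patient-level, which the article does not say. It also assumes that a positive FDG lesion always stays counted, a rule found nowhere. It gives no reliable size.

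**Conclusion.** The point holds in a limited form. As written, the stage-shift proportions measure disagreement between tracers and cannot show which one stages better. The size is indeterminate, not a known bias: an upstaging proportion of 14% at n = 50 is compatible with anything from a 14-point gain to a 14-point loss in correct staging, under the simplification that exactly one of the two stages is right in each shifted patient. The share of correct shifts is unknown before the data, and no value is claimed for it here.

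It would be wrong to conclude that the trial ignores pathology, since findings are checked against it. The gap is confined to the patient-level stage. In an exploratory trial with no test on this outcome, this is a worthwhile and inexpensive improvement, and does not undermine the design. The added/replacing wording is a minor clarification.

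**What to change.** 1. **Add a correctness table.** Where a surgical-pathological stage is available, classify every upstaging and downstaging as correct or incorrect. Report the paired difference in the proportion correctly staged, (b - c)/n, with a confidence interval, beside the planned proportions.
2. **Name the reference for each time point.** Use Group A surgical pathology for primary staging and interval-debulking pathology for post-NACT staging. Show separately any patient whose reference stage rests on the fallback sources, because for FAPI lesions these include FDG PET/CT itself.
3. **Align the wording.** In Primary objectives, replace the phrase about the added scan with wording that matches the replacement procedure in Study flow overview and in Staging and impact on patient management. Name one comparator, conventional imaging with FDG; at present it is given as conventional imaging including FDG in one place and FDG PET/CT in another.

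Cost: a few sentences and one further table from pathology already collected. FAPI scans are interpreted only after all patients are enrolled, so a change made before then precedes the results. The downside is that the primary-staging check covers about 25 of 50 patients. They are selected by a treatment allocation that uses the FDG result and not the blinded FAPI result, so the table should be labelled as applying to that subset.

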### Secondary objectives

The secondary objectives are as follows: (1) To estimate the proportion of patients hypothetically treated differently due to [^68^Ga]Ga-FAPI-46 PET/CT replacing [^18^F]FDG PET/CT; (2) to investigate the intensity of [^68^Ga]Ga-FAPI-46 uptake in tumor deposits; (3) to investigate the feasibility of FAPI PET/CT for chemotherapy-response assessment compared to FDG PET/CT; (4) to investigate the prognostic value of FAPI PET/CT compared to FDG PET/CT at primary staging and post-NACT staging; (5) to evaluate potential unexpected FAPI PET/CT findings; and (6) to evaluate the safety of [^68^Ga]Ga-FAPI-46 injections.

